### Sample size

Sample size was calculated using a web-based calculator (www.openepi.com). Results from a previous study using an ACL autologous reconstruction technique were used to define the control group [21]. The authors reported a postoperative increase in the Kujala score from 56.7 ± 17.7 (2×SD) to 86.8 ± 14.4 (2×SD). Success rates of isolated MPFL reconstruction are good, with patients reporting good or excellent outcomes of 87–96% [3, 21].

The minimally clinically important difference is defined as half of a standard deviation according to the method utilized by Norman et al*.* [37]. Using the result from Panni et al., we determined that σ = 7.2 in the treatment cohort, and therefore assumed a difference in 10 points would be clinically detectable and relevant.

Using a 1:1 enrolment ratio in a non-inferiority trial design, with beta of 0.2 and alpha of 0.05, a total of 30 patients will be required – 15 in each treatment arm. A Cohen’s *d* value of 1.01 with an effect size of 0.58 means that any significant difference attributable to the treatment received should be found using this sample size. Using the results of a previously published study [21], a minimum sample size of 10 patients – 5 in each arm – will be required in order to detect a clinical difference in the treatment groups.

Therefore, the aim is to recruit 15 patients in each group into this study, which allows for an attrition rate of up to 60% in each group. This will still allow meaningful statistical analysis to be performed. This is relevant due to the young age of the study population, which therefore has potential to be affected by population migration and loss to follow up. Clinical follow up will occur postoperatively at intervals of 3, 6, 12, 18 and 24 months.

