### Statistical analysis and trial end points

The intended data analysis will be on an intention-to-treat and per-protocol basis to demonstrate non-inferiority. This will allow bias between the treatment arms to be minimised, and demonstrate the efficacy of the intervention itself. Data analysis will be performed by one of the study investigators using SPSS v22 for Mac (IBM Inc., Armonk NY, USA), and will be verified by the local unit R&D department. Data will be tested for normality using the Shapiro Wilk test. Appropriate parametric and non-parametric tests will used accordingly.

Primary outcome measures will be compared between groups at set postoperative time points of 3, 6, 12, 18 and 24 months. Additionally, outcomes at these time points will be compared to preoperative baseline i.e. the analysis metric will be the change from preoperative baseline. This will allow calculation of change in patient-reported outcome scores at the set time points and the change in these reported scores over the study timeframe.

For primary and secondary outcome scores, the mean ± SD, median and range will be given for continuous data. For the secondary outcomes, the frequency of complications and all-reason revision will be recorded as a percentage and analysed by chi square analysis. For all tests, a *p* value <0.05 will be considered significant.

End points will be completion of the study timeframe (2 years), or further dislocation/all reason revision surgery. The trial will only be stopped should information become available that indicates that it is unethical to use synthetic grafts.

We propose to test non-inferiority using the intention-to-treat analysis set. No crossover of treatment arms will be allowed to occur as part of the protocol. Therefore, the study shall include all participants, as randomised. Patients will be reviewed at each specified time point as previously outlined. A single imputation model with last value carried over (LVCO) will be employed should patients drop out or be lost to follow up. The trial is designed to accommodate a 60% dropout rate, and still maintain a suitable sample size for meaningful statistical analysis.

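### The sample-size inputs are mutually incompatible: 10 points does not follow from the half-SD rule, and 15 per arm does not follow from 10 points with an SD of 7.2

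*Protocol article*

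**What the plan says.** All the sample-size inputs are in the Sample size section of the protocol article.

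- **Source of the SD.** A published autograft series, with the Kujala score rising "from 56.7 ± 17.7 (2×SD) to 86.8 ± 14.4 (2×SD").
- **MCID rule.** "The minimally clinically important difference is defined as half of a standard deviation".
- **SD and target.** From that series, "we determined that σ = 7.2 in the treatment cohort, and therefore assumed a difference in 10 points would be clinically detectable and relevant".
- **Design and error rates.** "Using a 1:1 enrolment ratio in a non-inferiority trial design, with beta of 0.2 and alpha of 0.05". The sidedness of alpha is not given.
- **Result.** "a total of 30 patients will be required – 15 in each treatment arm".
- **Standardised effect.** Cohen's d is given as a "value of 1.01 with an effect size of 0.58 means that any significant difference attributable to the treatment received should be found".

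The same section says that 5 per arm would be enough to detect a clinical difference. The section on statistical analysis and trial end points compares the arms at each postoperative visit and adds that "the analysis metric will be the change from preoperative baseline".

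**The concern.** The section gives an MCID rule, an SD, a target difference, a standardised effect and a sample size as one chain of reasoning. For two arms of equal size, any two of the difference, the SD and d fix the third, and d with alpha and beta fixes the number per arm. These figures do not fit that relation, so a reader cannot tell which difference the trial was sized for.

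This matters more in a trial meant to show non-inferiority, because the difference it can exclude is what gives the result its meaning. If the MCID is half an SD but the number of patients suits a difference of about one SD, a finding of no important difference could be taken to exclude far more than it does.

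**Working it through.** **Inputs (Sample size section).** SD 7.2 (14.4 halved, as the 2×SD label implies); difference 10 points; MCID 0.5 SD; d = 1.01; effect size 0.58; alpha 0.05, sidedness not stated; beta 0.2; 15 per arm.

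**Formula.** n per arm = 2(z_α + z_β)²/d², where d = difference/SD. With two-sided 0.05 (equivalently one-sided 0.025), (1.960 + 0.842)² = 7.85. With one-sided 0.05, (1.645 + 0.842)² = 6.18. For non-inferiority with no true difference, the margin takes the place of the difference. Powers below are from the noncentral t distribution.

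**1. The plan's own figure.** From d = 1.01, two-sided: 2 × 7.85/1.01² = 15.4, or 16 after rounding up, so 15 is approximately reproduced. One-sided 0.05 gives 2 × 6.18/1.01² = 12.1, or 13. The stated size therefore fits d = 1.01 at two-sided 0.05.

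**2. From the stated difference and SD.** d = 10/7.2 = 1.39. Two-sided: 2 × 7.85/1.39² = 8.1, or 9 per arm (9.2 by the t-test). One-sided 0.05: 6.4, or 7. Neither gives 15.

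**3. What d = 1.01 would require.** At 10 points, SD = 10/1.01 = 9.9. At SD 7.2, difference = 1.01 × 7.2 = 7.3 points. Neither figure is in the article.

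**4. The half-SD rule.** 0.5 × 7.2 = 3.6 points. Ten points is 10/3.6 = 2.8 times that. Taking the SD as 14.4 instead gives 7.2 points, which is still not 10.

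**5. The 0.58.** The article does not define it. As a standardised difference it contradicts 1.01 and would need 2 × 7.85/0.58² = 46.7, or 47 per arm. As a correlation, d = 1.01 corresponds to 1.01/√(1.01² + 4) = 0.45.

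**6. Power with 15 per arm (t-test).**

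| Difference | d | Two-sided 0.05 | One-sided 0.05 |
|---|---|---|---|
| 10 points, SD 7.2 | 1.39 | 96% | 98% |
| Stated d | 1.01 | 76% | 85% |
| Half-SD MCID, any SD | 0.50 | 26% | 38% |

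The normal approximation gives 79% two-sided at d = 1.01 and 28% at d = 0.5. For 80% power at d = 0.5, the formula gives 2 × 7.85/0.25 = 62.8, or 63 per arm (64 by t), two-sided.

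**7. What 15 per arm can detect with 80% power.** By formula, √(2 × 7.85/15) = 1.02 SD; by the t-test, 1.06 SD (two-sided 0.05 or one-sided 0.025). In points, 1.06 × 7.2 = 7.6. At one-sided 0.05 the formula gives √(2 × 6.18/15) = 0.91 SD.

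**8. Sensitivity to the SD label (assumption).** If ±14.4 in the cited study is one SD and not two, d = 10/14.4 = 0.69 and n = 32.6, or 33 per arm. Power with 15 per arm is then 45% (two-sided), and 1.06 SD is 15.3 points.

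**The case against.** A reader might infer that the trial has 26% power where the plan promises 80%. The article does not support that. It never claims 80% power at half an SD: its assumed difference is 10 points, which it calls detectable and relevant but does not call the MCID. At 10 points with SD 7.2, power is 96% and 15 per arm is more than enough; at d = 1.01 it is close to the 80% intended. The 26% also assumes two-sided 0.05, and one-sided 0.05 gives 38%. For the same reason the article does not establish that 63 or 64 per arm are needed.

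Three further inferences go too far:

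- **The 5-per-arm figure does not prove that 17.7 and 14.4 are full SDs.** It can be reached that way if the pre-to-post gain, 86.8 − 56.7 = 30.1, is used as the between-arm difference: 7.85 × (17.7² + 14.4²)/30.1² = 4.51, or 5. But SD 7.2 and 10 points without the two-sample factor of 2 also give 7.85 × 51.84/100 = 4.07, or 5. The article's own label is 2×SD.
- **Using a postoperative SD is not shown to be an error.** The arms are also compared at postoperative visits. With baseline SD 17.7/2 = 8.85, the SD of change exceeds 7.2 only if the pre-to-post correlation is below 8.85/(2 × 7.2) = 0.61, and no correlation is given.
- **The detection sentence is not untrue at every value.** It is reasonable at 10 points with SD 7.2 and fails for smaller differences.

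The conflict itself stands. If 10 points is the real target, it was not derived from the half-SD rule, and neither d = 1.01 nor 15 per arm follows from it.

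**Conclusion.** The concern holds as an internal contradiction. The half-SD rule gives 3.6 points at the stated SD, not 10. Ten points at that SD is d = 1.39 and about 9 per arm, not d = 1.01 and 15. At two-sided 0.05, 15 per arm fits only a d of about 1.01 to 1.06, which at 10 points means an SD near the unstated 9.9. The 0.58 has no definition and matches d = 1.01 on neither reading.

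The section's own inputs thus imply power anywhere from 26% to 96% two-sided, or 38% to 98% one-sided. The result at the half-SD MCID does not depend on which SD is right, because half an SD is d = 0.5 by definition. At that difference the trial would more often miss than find an effect under either sidedness, so the assurance about detecting any significant difference cannot stand unqualified. The figures of 33 per arm and 45% power apply only if the 2×SD label proves wrong, which the article alone cannot settle.

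**What to change.** Rewrite the Sample size section as follows.

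1. Check in the cited study whether ±14.4 is one SD or two, and use the confirmed value throughout.
2. State one target difference or non-inferiority margin, and say whether alpha is one- or two-sided.
3. Stop deriving 10 points from the half-SD rule, or justify 10 points independently.
4. State that 15 per arm gives 80% power only for about 1.06 SD (two-sided 0.05 or one-sided 0.025). Give this in points for the confirmed SD: 7.6 if it is 7.2, 15.3 if it is 14.4. If one-sided 0.05 is intended, recompute it.
5. Report the power at the half-SD MCID beside it: 26% at two-sided 0.05 or 38% at one-sided 0.05.
6. Delete the 0.58 and the sentence saying that any significant difference should be found.

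The cost is a rewording and one check of the source. Enrolment need not change. The downside is that the stated power becomes less favourable.

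### The minimum of 5 per arm matches no between-graft calculation tried on the protocol's own inputs, so the 60% attrition allowance built on it is unsupported

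*Protocol article*

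**What the plan says.** The Sample size section draws on one earlier autologous series, which serves to define the control group. It reports a "postoperative increase in the Kujala score from 56.7 ± 17.7 (2×SD) to 86.8 ± 14.4 (2×SD"). Halving 14.4, the protocol writes "we determined that σ = 7.2 in the treatment cohort" and "assumed a difference in 10 points would be clinically detectable and relevant". With alpha 0.05, beta 0.2, 1:1 allocation, a non-inferiority design and a Cohen's d of 1.01, it arrives at 15 per arm.

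It then returns to the same series and says that "a minimum sample size of 10 patients – 5 in each arm – will be required in order to detect a clinical difference" between the treatment groups. From this it concludes that recruiting 15 per arm is a plan "which allows for an attrition rate of up to 60% in each group". The section Statistical analysis and trial end points repeats the claim: "The trial is designed to accommodate a 60% dropout rate, and still maintain a suitable sample size for meaningful statistical analysis". That section also fixes change from the preoperative baseline as the analysis metric, and fills missing values by carrying the last value forward.

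**The concern.** The cited series followed patients treated with one technique. The figures taken from it describe a gain from before to after surgery and contain no contrast between grafts. A sample large enough to show that surgery raises the score can be very small, but it does not tell us how many patients are needed to compare two grafts that may both raise it.

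The section also sits uneasily with itself: it gives 15 per arm as required at beta 0.2, and then treats 6 per arm as enough.

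At stake is a stated property of the design. Readers are told that losing 9 of 15 patients in each arm leaves an adequate trial, in a young population that the protocol itself expects may be lost through migration. If that is wrong, 2-year retention looks less important than it is, and an inconclusive result could be presented as a planned and adequate one.

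**Working it through.** **Inputs (all from Sample size unless noted).** Preoperative 56.7 ± 17.7 and postoperative 86.8 ± 14.4, both ± values labelled 2×SD; planning SD 7.2; difference of interest 10 points; d = 1.01; power 0.80; alpha 0.05 with sidedness not stated, so both readings are shown; 15 per arm; attrition 60%. Metric: change from baseline (Statistical analysis and trial end points).

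**1. Reproducing 5 per arm.** The normal-approximation formula for two groups with unequal SDs is n = (SD₁² + SD₂²)(z₁₋α/₂ + z_power)² / Δ². Enter the before and after scores as two groups, with the ± values as full SDs:

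- Δ = 86.8 − 56.7 = 30.1
- SD₁² + SD₂² = 17.7² + 14.4² = 520.65
- (1.960 + 0.842)² = 7.849
- n = 520.65 × 7.849 / 906.01 = 4.51, rounded up to 5 per group, 10 in total

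This matches the stated figure. Reading the ± values as labelled (SDs 8.85 and 7.2) gives 1.13, or 2 per group. The match therefore needs the unhalved values, while the planning SD of 7.2 uses the halved one.

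**2. Between-graft requirement, normal approximation, 80% power.** n = 2·SD²(z_α + z_power)² / Δ².

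| Input | One-sided 0.05 | Two-sided 0.05 (or one-sided 0.025) |
|---|---|---|
| 10 points, SD 7.2 | 6.41 → 7 | 8.14 → 9 |
| d = 1.01 | 12.12 → 13 | 15.39 → 16 |
| 10 points, SD 14.4 | 25.64 → 26 | 32.55 → 33 |

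None gives 5. To have 80% power with 5 per arm, the arms would have to differ by 1.57 SD (one-sided 0.05) or 1.77 SD (two-sided), which is 11.3 or 12.8 points at SD 7.2. Both exceed the 10 points of interest.

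**3. Power after 60% attrition.** 15 × 0.4 = 6 per arm. The t-test has 10 degrees of freedom and noncentrality Δ / (SD·√(2/6)), which is 2.41 for 10 points at SD 7.2 and 1.75 for d = 1.01.

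| Input | One-sided 0.025 | One-sided 0.05 |
|---|---|---|
| 10 points, SD 7.2 | 58% | 72% |
| d = 1.01 | 35% | 49% |
| 10 points, SD 14.4 | 19% | 30% |

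For non-inferiority these are the powers to exclude a 10-point deficit (or one of 1.01 SD) when the true difference is zero.

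**4. The stated metric.** The SD of a change score is √(SD₁² + SD₂² − 2r·SD₁·SD₂). The pre/post correlation r is not given, so it is assumed here, with SDs 8.85 and 7.2 and a 10-point difference.

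| Assumed r | SD of change | Power at 6 per arm, one-sided 0.025 | One-sided 0.05 |
|---|---|---|---|
| 0 | 11.4 | 28% | 41% |
| 0.3 | 9.6 | 37% | 51% |
| 0.5 | 8.2 | 48% | 63% |
| 0.7 | 6.4 | 68% | 81% |

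**5. Attrition that 15 per arm could bear (t-test, 80% power).**

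- SD 7.2: 10 per arm at one-sided 0.025, so 1 − 10/15 = 33%; 8 per arm at one-sided 0.05, so 1 − 8/15 = 47%.
- d = 1.01: 17 per arm at one-sided 0.025, so no reserve; 13 at one-sided 0.05, so 1 − 13/15 = 13%.
- SD 14.4: no reserve; all 15 per arm give 45% or 58% power.

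**The case against.** **The origin of the 5 is not stated.** This stands. A reader might infer that the before/after comparison is proven to be the source. It is not: the protocol names the series but not the inputs. A one-sample formula with 10 points and SD 7.2 gives 7.2² × 7.849 / 100 = 4.07, which also rounds up to 5. The before/after route is the likelier one, because the sentence points to the series that supplies those scores. But neither route compares two grafts, so the conclusion does not depend on which was used.

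**The shortfall can be small.** This stands in part. At SD 7.2, one-sided 0.05 and the normal approximation, 6.41 per arm are needed, 6 remain, and power is 78%. With an assumed correlation of about 0.7 and one-sided 0.05, t-test power is 81%. It would therefore be too strong to say that 6 per arm can never reach 80%. But the protocol states neither the correlation nor a one-sided test.

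**Carrying the last value forward keeps all randomised patients in the analysis.** Only nominally. With 60% lost by 24 months, most 24-month values would be earlier ones carried forward, and the lost information is not restored.

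**A correction could replace one unsupported figure with another.** This stands. Declaring that the design tolerates 33% would rest on the postoperative SD rather than the SD of change, would ignore d = 1.01, and would supply a margin and a one-sided level that the protocol does not state. It calls 10 points relevant but does not name it as the non-inferiority margin.

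**Conclusion.** The 5-per-arm minimum is wrong as written: no between-graft calculation tried on the protocol's own inputs yields it. The 60% attrition allowance that rests on it is unsupported in both places. On the protocol's 10 points and SD 7.2, the 6 patients left per arm give 58% or 72% power by t-test; on its d of 1.01, 35% or 49%. The stated target is 80%. About 80% is reached only with an assumed correlation near 0.7 together with a one-sided 0.05 test.

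A reader might go further and conclude that 15 per arm is itself too few. The document does not settle that. With complete data, 15 per arm gives 96% power at SD 7.2 and one-sided 0.025, 76% at d = 1.01, and 45% if 14.4 is the true SD. Which applies depends on whether the ± values are SD or 2×SD, and the cited series is not at hand to decide it. What the ethics committee was told is not shown either, so nothing is claimed about that.

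**What to change.** Delete the 5-per-arm sentence and both 60% statements (Sample size; Statistical analysis and trial end points). Check the cited series to settle whether 17.7 and 14.4 are SD or 2×SD, and use one reading throughout.

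Then restate the attrition tolerance from the between-arm requirement for change from baseline, naming the SD of change (with its assumed correlation), the non-inferiority margin and the test level. Until these are fixed, show a range rather than a single figure: at SD 7.2, 33% (one-sided 0.025) or 47% (one-sided 0.05); at d = 1.01, none or about 13%; and, if the SD is 14.4, no reserve, with 45% or 58% power from all 15 per arm. Add that carrying values forward does not count towards the evaluable number.

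The cost is rewording in two sections and a less favourable stated tolerance. Correcting the statement needs no extra patients.

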### Outcomes

The primary outcome will be to determine the patient-reported outcome score using the validated Kujala score [32]. This is a validated scoring system designed specifically for patellar instability [32]. Scores will be collated preoperatively, and at the pre-defined postoperative time points of 3, 6, 12, 18 and 24 months. This will be identical for both autologous and synthetic reconstruction techniques. Specifically, we will report the change in the Kujala score at these set time points and analyse the data for differences between surgical techniques to determine if one appears to be superior. This will demonstrate the efficacy of the treatments under investigation, and allow a meaningful statistical comparison between the treatment arms.

Additional secondary outcomes scores will also be reported. These will be collected at the same time points as the primary outcome score, preoperatively and then postoperatively at 3, 6, 12, 18 and 24 months. The outcome scores will include the Tegner Activity Level Scale [33], Lysholm Knee Score [34], the Banff Patellar Instability Index (BPII) [35] and the anterior cruciate ligament (ACL) Quality of Life Score [36]. These scores have been previously validated and are reliable in assessing ligamentous injuries of the knee and are commonly reported in studies of ligamentous reconstruction.

Other secondary outcomes will include the incidence of complications and all-reason revision surgery. Those patients lost to follow up will have their data included up to this point to allow for analysis at the set postoperative time points. The aim is to have data on medium-term outcomes at 2 years for all participants.

At each study-review time point, participants will be questioned about adverse events attributable to undergoing surgical reconstruction of the MPFL that they have experienced since their previous review. This will include graft rupture/failure, synovitis, persistent instability and reoperation/revision surgery.

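### The stated tolerance of up to 60% attrition is not supported by the plan's own inputs, conflicts with its aim of 2-year data for all, and no means is described of obtaining the Kujala score from patients who move

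*Protocol article*

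**What the plan says.** The Sample size section of the protocol article sets the total: "a total of 30 patients will be required – 15 in each treatment arm". It gives a smaller figure, 5 per arm, as the minimum needed to detect a clinical difference, and says of recruiting 15 per arm: "which allows for an attrition rate of up to 60% in each group". The justification is that the study population is young and so "has potential to be affected by population migration and loss to follow up". The section Statistical analysis and trial end points repeats the assurance: "The trial is designed to accommodate a 60% dropout rate".

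On follow-up, the Sample size section says "Clinical follow up will occur postoperatively at intervals of 3, 6, 12, 18 and 24 months", and the analysis section adds "Patients will be reviewed at each specified time point as previously outlined". The Outcomes section defines the primary outcome: "The primary outcome will be to determine the patient-reported outcome score using the validated Kujala score". It also sets a retention aim: "The aim is to have data on medium-term outcomes at 2 years for all participants".

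The stated responses to loss are to keep the data gathered up to that point (Outcomes; Recruitment) and to carry the last value forward (Statistical analysis and trial end points).

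**The concern.** Two statements in the article pull apart: one wants 2-year data from everyone, the other presents the loss of more than half of each arm as something the design can bear. If the second is wrong, the trial could lose far more patients than it can afford while the team believes it is still within plan.

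The stated responses to loss all act after a score has gone missing, and no analysis recovers a score that was never collected. Moving away ends easy clinic attendance, but it need not end the supply of a patient-reported score. Observed 24-month scores would also reduce the risk that those who stop attending are mainly the patients who did well, or mainly those who did badly.

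**Working it through.** **Inputs (Sample size section).** 15 per arm; attrition up to 60%; minimum 5 per arm; alpha 0.05, sidedness not given; beta 0.2; σ = 7.2; difference 10 points; Cohen's d 1.01; source scores 56.7 ± 17.7 before and 86.8 ± 14.4 after surgery, with the spreads labelled as 2×SD. No separate non-inferiority margin is named, so the 10 points serve as the difference or margin.

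**1. Where the plan's figures come from.** With n per arm = 2(1.96 + 0.84)²/d²:
- d = 1.01: 2 × 7.85/1.0201 = 15.4, so 16 per arm. This is the input that comes close to 15 per arm.
- d = 10/7.2 = 1.39: 2 × 7.85 × 0.72² = 8.1, so 9 per arm.
- The 5-per-arm minimum was reproduced only by taking the before–after gain of 30.1 points (86.8 − 56.7) as the difference and 17.7 and 14.4 as full SDs: (17.7² + 14.4²) × 7.85/30.1² = 520.65 × 7.85/906.01 = 4.5, so 5. A before–after gain is not a difference between arms.

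**2. What 60% attrition leaves.** 15 × 0.4 = 6 per arm, or 12 of 30. The other 18 scores would be missing or carried forward. Six exceeds the stated minimum of 5, which appears to be why 60% was thought tolerable.

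**3. Power for 10 points** (noncentral t, 2n − 2 degrees of freedom, noncentrality d√(n/2)):

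| n per arm | Loss | SD 7.2, two-sided | d = 1.01, two-sided |
|---|---|---|---|
| 15 | 0% | 96% | 76% |
| 12 | 20% | 90% | 66% |
| 9 | 40% | 79% | 52% |
| 6 | 60% | 58% | 35% |

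At 6 per arm, a one-sided test at 0.05 gives 72% and 49%. The normal approximation at 6 per arm gives 67% two-sided and 78% one-sided at SD 7.2, and 42% two-sided at d = 1.01. All of these are below 80%.

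**4. Precision.** The 95% half-width is t(0.975, 2n − 2) × SD × √(2/n). At SD 7.2:
- n = 15: 2.048 × 7.2 × 0.365 = 5.4 points
- n = 12: 2.074 × 7.2 × 0.408 = 6.1 points
- n = 6: 2.228 × 7.2 × 0.577 = 9.3 points

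At d = 1.01 the SD is 10/1.01 = 9.9, and the half-widths are 7.4, 8.4 and 12.7 points.

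**5. Loss the plan could tolerate.**
- SD 7.2, two-sided: 9 per arm by the normal approximation (79% by t), or 10 per arm to clear 80% by t. Tolerable loss is 1 − 9/15 = 40% or 1 − 10/15 = 33%.
- d = 1.01, two-sided: 16 per arm are needed, so no allowance is left.
- One-sided at 0.05, normal approximation: 7 per arm at SD 7.2 (1 − 7/15 = 53%) and 13 per arm at d = 1.01 (1 − 13/15 = 13%). Even the most lenient of these does not reach 60%.

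**The case against.** A reader might infer more than the article says, and four stronger readings should be set aside.
- That the plan expects migration to remove 60% of patients. It does not: 60% is a ceiling for attrition from any cause, and migration is named as one potential cause.
- That the plan gives up its 24-month data needlessly. The Outcomes section aims for 2-year data on everyone.
- That scores are taken only in clinic. Reviews are scheduled, but the mode of score collection is not stated, and remote completion is neither described nor excluded.
- That all four secondary scores can be completed without attending. The article does not say so. The argument here rests on the Kujala score, which it does call patient-reported.

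It is also fair to say that contact details taken at consent, visit windows and similar procedures are commonly left to the full protocol, so their absence from an article is no defect. No single primary time point is named, so a patient who moves late still contributes earlier scores. And the power figures show the cost of having 6 rather than 15 per arm, not the benefit of remote collection, which cannot be quantified from the document.

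These points limit the finding but do not remove it. The 60% tolerance is stated outright in two sections, so it is not a detail left elsewhere, and the plan's own inputs contradict it. Carrying values forward keeps the nominal number at 15 per arm but adds no 24-month observations.

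**Conclusion.** The point holds in this form: the assurance that the design withstands 60% attrition is wrong on the plan's own figures and conflicts with its retention aim. At 6 per arm, two-sided power is about 58% at SD 7.2 and 35% at d = 1.01, against a planned 80%. At SD 7.2 the half-width grows from 5.4 to 9.3 points, nearly the whole 10-point difference. That no route is described to the Kujala score of a patient who moves is a supporting point only, since the full protocol may cover it.

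The results assume equal loss in both arms, analysis of observed scores at one time point, the plan's SD or d, and the sidedness shown. The conclusion is the same under each choice of sidedness. Correction is advisable and easy.

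**What to change.** 1. In Sample size and in Statistical analysis and trial end points, delete the statements that the trial accommodates 60% attrition. Alternatively, restate the tolerable loss from the plan's own inputs: about 33–40% at SD 7.2 and none at d = 1.01 (both two-sided), saying which input and sidedness apply. Drop the 5-per-arm minimum as the basis for any allowance.
2. Set complete 24-month Kujala data as the target, in line with the aim already in Outcomes.
3. State that when a review is missed, the Kujala score is sought by post, telephone or online and the mode recorded. Count a patient as lost only after no response by any route.

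The cost is a wording change and a few reminder contacts for 30 patients. Changes in trial design go to the R&D department and the ethics committee under the plan's own rules. The downside is a possible mode effect, which the recorded mode allows to be examined. How much retention would improve is an assumption: if loss were held to 20%, power would be 90% at SD 7.2 and 66% at d = 1.01.
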